## Abstract

**Background:**

Lack of trust in parental support is a transdiagnostic risk factor for the development of psychological problems throughout the lifespan. Research suggests that children’s cognitive attachment representations and related information processing biases could be an important target for interventions aiming to build trust in the parent-child relationship. A paradigm that can alter these biases and increase trust is that of Cognitive Bias Modification (CBM), during which a target processing bias is systematically trained. Trust-related CBM training effects could possibly be enhanced by oxytocin, a neuropeptide that has been proposed to play an important role in social information processing and social relationships. The present article describes the study protocol for a double-blind randomized controlled trial (RCT) aimed at testing the individual and combined effects of CBM training and oxytocin administration on trust in maternal support.

**Methods/design:**

One hundred children (aged 8–12 years) are randomly assigned to one of four intervention conditions. Participants inhale a nasal spray that either contains oxytocin (OT) or a placebo. Additionally, they receive either a CBM training aimed at positively modifying trust-related information processing bias or a neutral placebo training aimed to have no trust-related effects. Main and interaction effects of the interventions are assessed on three levels of trust-related outcome measures: trust-related interpretation bias; self-reported trust; and mother-child interactional behavior. Importantly, side-effects of a single administration of OT in middle childhood are monitored closely to provide further information on the safety of OT administration in this age group.

**Discussion:**

The present RCT is the first study to combine CBM training with oxytocin to test for individual and combined effects on trust in mother. If effective, CBM training and oxytocin could be easily applicable and nonintrusive additions to interventions that target trust in the context of the parent-child relationship.

**Trial registration:**

ClinicalTrials.gov, ID: NCT02737254. Registered on 23 March 2016.

**Electronic supplementary material:**

The online version of this article (doi:10.1186/s13063-017-2077-2) contains supplementary material, which is available to authorized users.

## Background

Lack of trust in parental support puts children at risk for the development of psychological problems across the lifespan [1, 2]. Bowlby [1] proposed that whether children are able to develop trust in parental support depends for a significant part on children’s experiences of care in response to distress during interactions with their parents. Through repeated interactions with sensitive and responsive parenting, children develop trust in the parent and become securely attached [3]. Conversely, when children experience recurrent insensitive, unresponsive or inconsistent parenting, they will have difficulty to develop trust in the parent and become insecurely attached [3]. Research suggests that up to 40% of the children are insecurely attached [4], and although insecure attachment is neither a necessary nor a sufficient cause for psychopathology development, it is considered an important transdiagnostic risk factor [5–7].

Given the risks associated with insecure attachment, there is need for effective interventions that can promote trust in the context of the parent-child relationship [8, 9]. The present study aims to investigate the individual and combined effects of a cognitive and a pharmacological intervention, specifically Cognitive Bias Modification (CBM) training and intranasal oxytocin (OT), on trust in maternal support. Although trust is important for psychological wellbeing across the lifespan, in the current study we focus on middle childhood (age range 8–12 years). Middle childhood has been proposed to be an important period for cognitive trust development, during which trust-related expectations can still relatively easily be influenced by new experiences [10, 11]. This suggests that middle childhood might be a sensitive period for interventions targeting trust in parental support. As a proof-of-principle test of the hypothesis that OT and CBM training can contribute to trust development in middle childhood, the current study aims to explore the effects of the (combination of) interventions within a sample of normally developing middle childhood participants. If the interventions prove effective in increasing trust, they could be a valuable addition to clinical interventions targeting trust in parental support.

Existing early childhood attachment-related interventions mostly focus on enhancing parental sensitivity and parents’ mental representations of the attachment relationships with their own parents [9, 12]. However, theory and research point to the importance of children’s own cognitive attachment representations and related information processing biases for repairing breaches in trust [1, 13]. More specifically, it has been shown that information regarding the parent is attended, interpreted and remembered in congruence with children’s attachment-related expectations [14–16]. As a result, interventions focusing solely on improving parenting skills might be less effective when children have insecure expectations. That is, if parents alter their behavior to be more sensitive and responsive, children who lack trust might not be able to adequately encode their parents’ retrained behavior because their insecure expectations were not altered. In support of such claims, research indicates that effect sizes of parenting training are small to moderate [17]. Moreover, effect sizes decrease when children’s age increases [18, 19], suggesting that parenting training has less impact when attachment-related information processing becomes increasingly insecure in response to prolonged exposure to insensitive and unresponsive parenting. Therefore, attachment processing biases could be an important additional target for interventions that aim to build or restore trust between parent and child.

A promising paradigm to change the way that information is processed and encoded is that of CBM [20]. CBM procedures aim to modify information processing styles by systematic practice of a target processing bias [21]. For anxiety disorders, among others, the CBM method has been shown effective in changing selective information processing biases and reducing disorder symptoms [22]. Recently, a CBM training paradigm was developed for children aged 8–12 years with the purpose to modify children’s interpretation of attachment-related information [23]. De Winter et al. [23] tested the effectiveness of this attachment-related CBM training. In their study, half of the participants received a CBM training, during which children were trained to securely interpret story scenarios that were ambiguous as to whether mother provided support. The other half of the participants received a neutral placebo training in which resolutions of ambiguity were not related to maternal behavior. Results showed that the CBM procedure was effective. That is, children in the CBM training condition showed an increase in secure interpretation bias and a decrease in insecure interpretation bias as compared to children in the neutral training condition. Importantly, trust was causally affected by attachment-related interpretation bias, as indicated by a significant increase in trust in the CBM training condition [23]. These results suggest that the CBM paradigm has therapeutic potential in the context of insecure attachment and lack of trust, as it could help build or restore children’s trust in their parents’ availability. An important next step towards the implementation of CBM as an intervention procedure is to identify the parameters that can increase the effectiveness of CBM [22].

A possible candidate for augmentation of the effects of CBM is the neuropeptide OT. Endogenous OT is synthesized in the hypothalamus, while exogenous OT can be noninvasively administrated in humans by means of a nasal spray. Functional brain imaging studies have shown that intranasal OT can modulate activity in, and connectivity between, brain regions involved in social cognition [24–26]. Overall, studies have shown that OT can help form, restore or maintain social relationships. As a result, OT has been proposed as a possible (addition to) treatment of disorders characterized by socioemotional difficulties [27]. For the current study, we propose that OT could enhance CBM effects on two levels, in accordance with the two-level model of OT effects on social behavior and social cognition as proposed by Quintana et al. [28]. First, on a behavioral level, OT has been shown to increase trust in social interaction [29] and improve attachment security [30, 31]. Therefore, OT could independently have an effect on the trust- and attachment-related outcome measures targeted by the current CBM training. Second, research suggests that OT can increase the salience and reinforcing value of socially relevant stimuli [32, 33] and enhance the processing of social information (see [34], and also [35] for neural evidence in rodents). Since the scenarios in the CBM training all describe social situations in which children might need their mother’s support, we hypothesize that OT might improve the processing of these scenarios. This way, OT could increase learning during CBM training, resulting in an additive effect of OT and CBM training on trust and trust-related outcome measures in the current study.

In pediatric populations, the majority of the limited number of OT studies has targeted children diagnosed with autism spectrum disorder (ASD) and these studies yielded mixed results [24, 36–39]. However, the scope of OT as potential therapeutic intervention reaches beyond the social problems associated with ASD [40]. Moreover, most OT studies in children were limited in sample size and sample selection. Therefore, researchers generally agree that OT’s precise role and (additive) value need further investigation [40, 41].

## The present study: aims and hypotheses

In the current study, participants administer a nasal spray that either contains OT or a placebo (PL). Additionally, they receive either a CBM training aimed at positively changing trust and related interpretation bias or a neutral training that is conjectured to have no trust-related effects. The aim of the present study is to test the main and interaction effects of CBM training and OT on three levels of trust-related outcome measures in middle childhood: trust-related interpretation bias; self-reported trust; and children’s trust-related behavior towards mother.

At the first level, we investigate the effects of CBM training, OT and both interventions combined on secure attachment interpretation bias and insecure attachment interpretation bias, as compared to no intervention (i.e., neutral training and PL). Based on the study by De Winter et al. [23], we expect that participants who receive CBM training show an increase in secure interpretation bias and a decrease in insecure interpretation bias as compared to children who receive no intervention. Since this is the first study examining the effects of OT on attachment interpretation bias, it is an empirical question as to what the effect of OT on interpretation bias is. When OT has a positive effect on interpretation bias, this should be reflected in increased secure interpretation bias and decreased insecure interpretation bias for children receiving OT as compared to no intervention. Given the proposed role of OT in improving the salience and processing of social stimuli [32, 34], intranasal administration of OT could enhance processing of the social stimuli presented in the CBM training and thereby increase its effectiveness. When joint exposure to CBM training and OT is beneficial, children in the combined intervention condition should show increased secure interpretation bias and decreased insecure interpretation bias as compared to participants who receive only one of the interventions.

At the second level, the effects of CBM training, OT, and both interventions combined on change in self-reported trust from pre-intervention to post-intervention are assessed. It is expected that participants who receive any intervention (CBM training, OT, or the two combined) will show an increase in trust as compared to participants receiving no intervention [23, 29]. If joint exposure to the two interventions is beneficial, this should be reflected in a stronger increase in trust for participants who receive the interventions combined as compared to participants who receive only one of the interventions.

At the third level, intervention-related changes in behavior of children towards mother and mother-child interactional behavior during a distressing task are observed. The main effects of the two interventions as well as the interaction effect of the interventions are assessed. To our knowledge this is the first study examining the effects of CBM training and OT on behavior during mother-child interaction. Nevertheless, previous studies have linked more trust to more positive behavior of child towards mother [42] and to a more coherent mother-child interactional pattern [43]. Therefore, if the interventions affect trust and these effects extend to the behavioral level, children who receive any intervention (CBM training, OT, or the two combined) should show an increase in positive approach towards mother as compared to children who receive no intervention. Similarly, mother-child dyads in the intervention groups (CBM training, OT, or the two combined) should show increased interactional coherence compared to mother-child dyads in which children receive neutral training and PL as a control condition.

Although the main goal of the current study is to test the effects of CBM training and OT on the abovementioned trust-related outcome measures, we plan to take the opportunity to carry out some additional explorative analyses. More specifically, we plan to test whether differences in participant characteristics moderate the effects of the interventions in the present study. This is especially relevant for the OT intervention, since accumulating evidence suggests that the effects of intranasally administered OT can be influenced by a variety of factors [44], including among others caregiving experiences [26, 45], social functioning [46], and (early) adverse events [47]. Since the present study is the first to test the effects of OT, as individual intervention and combined with CBM, on trust-related outcomes in middle childhood, it is an opportunity to explore the effects of participant characteristics to inform future research about possible factors to take into account when administering OT as an (additive) intervention. Importantly, we also closely monitor the side-effects of a single administration of OT in middle childhood to provide further information on the safety of OT administration in this age group.

## Methods/design

### Study design

The current study is a double-blind randomized controlled trial (RCT). The trial has a 2 × 2 factorial design, which combines the active and placebo interventions resulting in four equally sized intervention groups: (1) CBM training and OT (both interventions), (2) CBM training and PL (cognitive intervention only), (3) neutral training and OT (pharmacological intervention only) and (4) neutral training and PL (no intervention). The current study design allows assessment of the effects of each intervention separately and of both interventions combined.

The pharmacy of the University Hospital of Heidelberg, Germany, carried out the randomization of the nasal sprays using RITA software version 1.30 [48]. They stratified randomization by training condition and used permuted blocks within strata [49]. The bottles containing OT nasal spray and PL look identical and the pharmacy of the University Hospital of Heidelberg numbered all nasal sprays. For each nasal spray number, a sealed envelope contains a piece of paper that connects the spray number to one of the interventions. Additionally, all envelopes contain a black piece of paper to prevent visibility of intervention allocation without opening the envelope. We assign the numbered nasal sprays to consecutive participants in sequential order, with training condition alternated between participants. Since both interventions are placebo-controlled, participants are blind to the intervention condition that they are in. Experimenters are aware of the training condition, but blind to the nasal spray condition. To conceal intervention allocation and maintain blinding, we do not open the envelopes until after data collection is finished. Only in case of severe adverse events, it is possible to open a sealed emergency unblinding envelope to unblind the medication for a given participant. We assess children’s awareness of the experimental condition (i.e., both the training and the nasal spray condition) that they are in at the end of the procedure. Furthermore, we assess experimenter’s and mother’s awareness of the nasal spray condition at the end of the procedure and 24 h after the procedure, respectively. The mother-child dyad is given a participant number that we use on all data documents. A separate password-protected document links participant names to participant numbers. In case of severe adverse events after nasal spray administration, the procedure can be discontinued. Moreover, mother and child can withdraw from the study at any time without giving a reason.

The trial takes place at the Parenting and Special Education Research Unit, KU Leuven, Belgium. The Medical Ethics Committee UZ KU Leuven/Research (S57012) approved the study design in accordance with the Declaration of Helsinki. We submit any protocol amendments and progress reports to the Ethics Committee as required, as well as an end-of-study declaration. We registered the trial in the database of ClinicalTrials.gov (NCT02737254). The Belgian Federal Agency for Medicines and Health Products also approved the trial. See Additional file 1 and Table 1 for a checklist and an overview of study procedures in line with Standard Protocol Items: Recommendations for Interventional Trials (SPIRIT) [50] and Additional file 2 for a description of all items from the World Health Organization Trial Registration Data Set.

**Table 1 Tab1:** Schedule of enrollment, interventions and assessments in line with Standard Protocol Items: Recommendations for Interventional Trials (SPIRIT)

	Study period				
	Enrollment	Allocation	Post-allocation		
Timepoint	Before intervention (baseline)	0	During intervention	Immediately after intervention	24 h after intervention
Enrollment:					
Eligibility screen	X				
Informed consent	X				
Allocation		X			
Interventions:					
CBM training + OT			X		
CBM training + PL			X		
Neutral training + OT			X		
Neutral training + PL			X		
Assessments:					
Interpretation speed of secure and insecure scenario resolutions			X		
Secure interpretation bias	X			X	
Insecure interpretation bias	X			X	
Trust (PIML)	X			X	
Puzzle task	X			X	
Mood	X		X	X	
OT side-effects				X	X
Mother-reported questionnaires:					
Demographic questionnaire			X		
Child temperament (EATQ-R)			X		
Child behavioral and emotional problems (CBCL)			X		
Parenting questionnaires (VSOG, subscales LAPPS, POPS, PCS)			X		
Pubertal development (PDS)			X		
Symptoms of sino-nasal problems (Snot-20)			X		

*CBCL* Child Behavior Checklist, *EATQ-R* Early Adolescent Temperament Questionnaire-Revised, *LAPPS* Louvain Adolescent Perceived Parenting Scale, *OT* oxytocin, *PCS* Psychological Control Scale, *PDS* Pubertal Developmental Scale, *PIML* People In My Life, *PL* placebo, *POPS* Perceptions of Parents Scale, 20-*Snot-20* 20-item Sino-Nasal Outcome Test, *VSOG* Verkorte Schaal Ouderlijk Gedrag

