## Discussion

Given the association between lack of trust in the parent and a wide range of psychopathological problems across the lifespan, there is need for interventions that can help build trust in parent-child dyads. The present article describes the protocol for a study that aims to test the individual and combined effects of two interventions – CBM training and intranasal OT – on children’s trust-related information interpretation bias, trust in maternal support, and observed mother-child interactional behavior. To this purpose, children are administered a nasal spray that contains either OT or PL. In addition, they receive either a CBM training aimed at positively changing trust and related interpretation bias or a neutral training that aims to have no trust-related effects. The different outcome measures are administered pre- and post-intervention to allow assessment of change due to the interventions.

The present study is the first study to combine intranasal OT administration with a CBM training procedure. Both individually and combined, the two interventions could exert effects on trust. The current study’s factorial design allows for assessment of these combined and individual effects of CBM training and OT. Other strengths are the double-blind and randomized design of the trial, reducing the risk of bias. Moreover, to our knowledge, the current trial is the first OT study in general-population, middle-childhood children with sufficient power to detect moderate OT effects.

In line with this, an important additional aim of the present study is to increase our knowledge of adverse events or side-effects associated with OT administration in pediatric populations. To date, limited data is available on the side-effects of OT in children, due to a small number of studies performed with limited sample sizes [40]. In the present study, the side-effects of OT are monitored in a relatively large sample of middle-childhood children, both at the end of the procedure and 24 h after intervention. The current trial can thus provide more insight into any side-effects associated with single-dose OT in middle-childhood children, which is an important step towards the use of OT as an intervention in pediatric populations.

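### CBM versus neutral training is alternated, not randomised, and experimenters know it, so the unqualified randomised and double-blind claims hold only for the nasal spray

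*Protocol article*

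**What the plan says.** All references are to the protocol article.

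- **What is randomised.** Under Study design, the pharmacy "carried out the randomization of the nasal sprays using RITA software version 1.30", and "They stratified randomization by training condition and used permuted blocks within strata". Training condition enters this step as a stratification factor.
- **How training is allocated.** The same section states: "We assign the numbered nasal sprays to consecutive participants in sequential order, with training condition alternated between participants".
- **What is concealed.** "For each nasal spray number, a sealed envelope contains a piece of paper that connects the spray number to one of the interventions". The envelopes hold spray content and nothing about training.
- **Who is blind.** "Experimenters are aware of the training condition, but blind to the nasal spray condition". For the children: "Since both interventions are placebo-controlled, participants are blind to the intervention condition that they are in". The section on observed behaviour during the puzzle task adds that video coders are blind to both factors.
- **What is claimed.** The Abstract says that children "are randomly assigned to one of four intervention conditions". Study design opens by labelling the study a double-blind randomised controlled trial. The Discussion says: "Other strengths are the double-blind and randomized design of the trial, reducing the risk of bias". None of the three limits the claim to the spray.

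**The concern.** Testing CBM is one of the two main purposes of the factorial design. Its main effect compares two groups of children formed by a deterministic rule that the testing staff can follow. Two routes to bias open up.

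The first is selection. If anyone who influences the order in which children enter knows whose turn it is, the training groups can differ systematically. The second is experimenter influence. The experimenter supervises the session and gives the puzzle instructions before and after the intervention while knowing the training condition.

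The planned awareness checks do not cover the second route for training, because experimenters and mothers are asked only about the spray. A reader who relies on the Abstract or Discussion would give the CBM result the same protection as the oxytocin result, which the Study design section does not support.

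**Working it through.** **1. The passages side by side.** Stratified blocks decide oxytocin or placebo within each training level. They do not decide who receives CBM; alternation does. No random start and no concealment of the training sequence is described. So the statements on allocation method contradict the general claim of random assignment to four conditions, and stratification does not remove the contradiction.

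**2. Predictability of the next training condition.** Under alternation it is 100% once one allocation is known. For comparison, the best guess was simulated for a randomised training list of 100 children (4,000 runs). It is right about 71%, 66% or 64% of the time with blocks of 4, 8 or 12, and 50% under simple randomisation. These block sizes are assumptions, since the article gives none.

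**3. The plan's own sample size.** Inputs from Sample size: *f* = 0.30, alpha 0.05, numerator df 1, four groups. Noncentrality is *f*²N with N − 4 denominator df.
- N = 90: noncentrality 0.09 × 90 = 8.1, critical F 3.95, power 0.8035. This is the smallest N that reaches 0.80.
- N = 100: noncentrality 0.09 × 100 = 9.0, critical F 3.94, power 0.8437.

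Both stated figures (90, and 0.84 at 100) reproduce. The allocation method does not enter them.

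**4. Effect of an assumed shift on the CBM main effect.** With 50 children per training level, the standard error of the contrast is √(1/50 + 1/50) = 0.20 SD. A shift of δ SD in the change score gives noncentrality δ/0.20 on 96 df, with critical |t| about 1.985.

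| Assumed shift δ | Noncentrality | Type I error |
|---|---|---|
| 0 | 0 | 5% |
| 0.1 SD | 0.5 | 7.9% |
| 0.2 SD | 1.0 | 16.8% |
| 0.3 SD | 1.5 | 31.8% |

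The planned effect is 2 × 0.30 = 0.6 SD, so a shift of 0.1 or 0.2 SD is one sixth or one third of it.

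**5. Effect on the other two tests.** Suppose the shift δ applies to every child at the CBM level, whatever the spray. The oxytocin-minus-placebo difference at that level contains δ − δ = 0, so neither the oxytocin main effect nor the interaction (the difference between two such differences) moves. A simulation with δ = 0.2 SD and 25 per cell agrees: rejection was about 16% for the CBM main effect, 5.1% for the interaction and 5.2% for oxytocin.

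**The case against.** The strongest reply is that the method is openly disclosed, the study is a proof of principle in normally developing children, and several safeguards remain. Children are blind to both factors and asked about both. Coders are blind to both. The experimenter leaves the room during the puzzle. Interpretation data are saved automatically, and trust is the child's own rating. Baseline differences in the outcome measures are to be tested. All this stands, and it limits the room for biased measurement. It does not make an alternated allocation random or concealed, and experimenter influence through instructions and the testing setting remains possible.

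Four stronger readings might be inferred, and the documents do not support them.

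- *The interaction is as exposed as the CBM main effect.* It is not. Spray is randomised within each training level, so an additive shift cancels. The interaction is distorted only if the trait on which children were selected also modifies the oxytocin effect.
- *Allocation is known for certain when the mother is telephoned.* The article does not say that the staff who screen and book are those who test, and it does not describe how bookings and no-shows affect the order. Predictability near the session is supported; certainty at the phone call is not.
- *The trial is effectively unblinded for CBM.* Participants and coders are blind; the experimenters are not.
- *Bias has occurred.* Nothing shows this. A shift of 0.2 SD would need, for example, 5 of 50 children per arm steered in opposite directions, each by 1 SD in expected change (5/50 × 1 × 2). That is demanding, because the listed eligibility criteria are factual and trust is first measured after arrival.

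**Conclusion.** The point holds for the CBM factor. Training is allocated by a predictable rule known to experimenters, so the CBM main effect is quasi-randomised. For that factor the accurate description is participant- and coder-blind with experimenters unblinded. The unqualified claims in the Abstract, Study design and Discussion are wrong to that extent. The oxytocin main effect keeps its randomised basis, and the interaction largely does, subject to the effect-modification condition above.

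The size of any bias cannot be known from the article. The rise in type I error to about 8% or 17% depends entirely on an assumed shift of 0.1 or 0.2 SD and serves only to show scale.

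**What to change.** 1. **Correct the text.** State that the spray is randomised, with experimenters blind to it. State that training is alternated, with participants and coders blind and experimenters unblinded. Report the CBM effect for children so allocated as quasi-randomised. This is needed whatever else is done.
2. **Change allocation for children still to be enrolled.** Trial status says recruitment is open. Draw training from a concealed computer-generated list with random block sizes, and reveal it only after the baseline tasks. Take the next numbered spray from the matching training stratum, which keeps the pharmacy's randomisation. Where feasible, let the program load the training version from the participant number so that the experimenter does not see it.
3. **If allocation changes mid-trial,** give the CBM effect by allocation phase, with a training × phase term, as a sensitivity analysis. A phase main effect alone adjusts for a period difference and neither detects nor removes bias in the training contrast.

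The cost is one list, a change to the training program, a short amendment for the approving bodies and a mixed allocation history to report. The gain from step 2 depends on how many children remain, which the article does not give. The sample size stays at 100.
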